### Participant withdrawal

Patients will be excluded from the trial if they or their next-of-kin withdraw their consent. As a result, the investigator will immediately interrupt treatment administration.

If the patient does not object to information on the primary outcome measure being obtained, the data will be collected and analysed. The data will be fully erased if the patient refuses this permission.

### Protocol suspension and severe adverse reactions

The treatment could be discontinued:Temporarily if:○ Renal clearance falls below 15 ml/min without haemodialysis support○ Liver tests (amino-transferase enzymes) are more than 20 times the normal○ Heart rate falls below 50 BPM with haemodynamic consequencesDefinitively if:○ Allergic symptoms appear○ Heart rate falls below 35 BPM whatever the haemodynamic profile○ Non-reactive uni/bilateral mydriasis develops○ Patient has a seizure in the ICU○ Patient has a stroke in the ICU with computed tomodensitometry (CT) scan confirmation○ Eyes not open 72 h after total sedation is interrupted

### Statistics

We hypothesised that baclofen administration can reduce the incidence of patients with at least one complication of agitation, using a two-sided test with an α of 5 % and 80 % power, from 42 to 27 %. This hypothesis in the placebo group is based on personal data. As a result, 314 patients are needed. Our study will include patients whatever their severity. Some patients may die before sedation interruption thus altering the power of the study. We therefore plan an interim analysis (after 50 % of inclusions), to adjust the sample size to maintain the statistical power. Friede and Kieser’s method [27, 28] allows both the initial hypothesis and the type-1 error planned a priori to be maintained. The analysis will be stratified at the participating centres. Statistical analysis will take place on an intention-to-treat principle. For the primary outcome, a logistic regression model will be applied to compare the proportion of agitation between the two treatment arms. Two sensitivity analyses will be performed and will consider dead patients to be without agitation, or as patients with or without agitation. A per-protocol analysis will also be performed to exclude patients with any of the exclusion criteria or without the inclusion criteria, or patients with incomplete treatment administration.

For the secondary outcomes, a Poisson regression model will be applied to compare the number of adverse events related to agitation, between the two treatment arms. Both length of ICU stay and mechanical ventilation will be compared with a log-rank test. Logistic regression will be used to compare binary qualitative secondary endpoints.

Normally distributed variables will be expressed as mean and standard deviation; nonnormally distributed variables will be expressed as median and interquartile range. Categorical variables will be expressed as numbers and percentages.

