## Methods/design

### Design

BACLOREA is a prospective, multicentre, double-blind, randomised controlled study versus placebo, performed in at-risk drinkers according to NIAAA criteria. We will assess the superiority of baclofen compared to placebo in preventing restlessness-related complications. The randomisation sequence will be computer-generated and stratified at the 11 participating centres. This study follows the international recommendations for interventional trials (see the SPIRIT checklist in Additional file 1).

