### Randomisation and blinding

The clinicians will perform screening, enrolment and randomisation. Randomisation is centralised, web-based and accessible 24 h a day according to the allocation list on https://www.dirc-hugo-online.org/csonline/. Randomisation will be stratified at the centres using a fixed block size of 1:1 and a randomisation number will be allocated to each patient. Baclofen and placebo will be prepared and ‘blinded’ at Nantes University Hospital pharmacy. The independent trial statistician, patients, clinicians and nurses will be blinded for the allocation of treatment.

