### Track record

Data will be recorded in the web-based electronic case report form (eCRF) by trial site staff. Characteristics at baseline will be gathered: age, site of inclusion, sex, weight, height, medical history, reason for ICU admission, alcohol consumption, kidney function, Simplified Gravity Index (IGSII) and Sequential Organ Failure Assessment (SOFA) scores on admission. During ICU hospitalisation we will assess: cumulative doses of all sedative drugs, agitation and alcohol withdrawal scores, agitation-related adverse events, blood tests results regarding alcohol test on admission, liver function tests and blood count during treatment, acquired infection, length of ICU stay, mechanical ventilation and whole hospitalisation. To preserve confidentiality of participant’s personal information, data will be key-coded using alphanumerical numbers. To minimise missing data, primary and secondary outcome will be notified daily. Patients will be monitored until day 90 and a supplemental telephonic contact will promote complete follow-up.

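### The stated primary model names centre as its only adjustment factor; adding a few baseline covariates that are already collected could raise power at almost no cost

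*Protocol article*

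**What the plan says.** The Statistics section of the protocol article states that "a logistic regression model will be applied to compare the proportion of agitation between the two treatment arms", and adds: "The analysis will be stratified at the participating centres". This matches the randomisation, which the Design section describes as "stratified at the 11 participating centres". No further term is named for the primary model, and none is excluded.

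The Track record section lists the baseline data. Besides age and sex, these include "alcohol consumption, kidney function, Simplified Gravity Index (IGSII) and Sequential Organ Failure Assessment (SOFA) scores on admission". The article gives these variables no role in the primary analysis.

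The sample size is a comparison of two proportions, 42% against 27%, "using a two-sided test with an α of 5 % and 80 % power", from which "314 patients are needed". The same section plans a sample size review after half of the inclusions, because deaths before sedation is stopped may affect power.

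**The concern.** Two of the recorded variables have a plausible link to the outcome in the article's own account. The Background connects alcohol abuse, through neurological damage, with a raised risk of restlessness. The Inclusion criteria set only a lower limit on intake, so intake may vary widely among those enrolled. As for severity, the Statistics section expects some patients to die before sedation is interrupted, and a patient who never wakes can hardly have most of the component events.

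If such variables are prognostic, a model that includes them tests the treatment effect with more power at the same number of patients, and it allows for chance imbalance between the arms. The planned power is 80% with almost no margin, and the plan's own protection for power is to change the sample size. Covariates already in the case report form might supply some of that protection without recruiting anyone.

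**Working it through.** **Inputs from the protocol article**
- Two-sided α of 5%, power 80%, rates 0.42 and 0.27, total 314 (Statistics).
- The placebo rate has no cited source: "This hypothesis in the placebo group is based on personal data". No prognostic strength is given for any baseline variable.
- Equal allocation within centre (Randomisation and blinding). Eleven centres (Design and Trial status; the abstract says twelve, which does not matter for this calculation).

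**Step 1: reproduce 314.** With the pooled-variance formula and no continuity correction, the mean rate is (0.42 + 0.27)/2 = 0.345, and

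n per arm = [1.960·√(2·0.345·0.655) + 0.842·√(0.42·0.58 + 0.27·0.73)]² / 0.15² = (1.318 + 0.559)² / 0.0225 ≈ 156.5, rounded up to 157.

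The total is 314, an exact match. Power at 157 per arm is 80.1%. The target is met without any covariate.

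**Step 2: approximate gain from adjustment.** Let R² be the share of outcome variance explained by the baseline covariates. The effective size per arm is then about 157/(1 − R²). R² is an assumption throughout.

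| Assumed R² | Effective n per arm | Power at 314 |
|---|---|---|
| 0 | 157.0 | 80.1% |
| 0.02 | 160.2 | 80.9% |
| 0.05 | 165.3 | 82.1% |
| 0.10 | 174.4 | 84.1% |
| 0.15 | 184.7 | 86.1% |
| 0.20 | 196.2 | 88.1% |
| 0.30 | 224.3 | 91.9% |

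**Step 3: simulation.** 314 patients, 11 centres, marginal rates 42% and 27%, no centre effect, one normal score standing for the covariates jointly, Wald test of treatment, 3000 trials per row.

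| Assumed AUC (R²) | Treatment + centre | With covariate | Gain (points) |
|---|---|---|---|
| 0.58 (0.02) | 81.9% | 82.2% | 0.3 |
| 0.63 (0.05) | 80.7% | 83.3% | 2.6 |
| 0.70 (0.11) | 81.3% | 85.0% | 3.7 |
| 0.74 (0.16) | 81.7% | 87.6% | 5.9 |
| 0.81 (0.28) | 79.7% | 90.3% | 10.6 |

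The Monte Carlo standard error of each power is about √(0.8·0.2/3000) = 0.7 points, so the gain in the first row cannot be told from zero.

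A second simulation used four independent covariates, a centre random effect with SD 0.3 and 4000 trials per scenario. It gave 81% to 83% at AUC 0.63, 82% to 86% at 0.69, 81% to 86–87% at 0.74 and 81% to 89% at 0.78. The two agree.

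**Step 4: the downside.** With six covariates of no predictive value, power was 80.6% with centre only and 80.4% with the covariates added. With no treatment effect (42% in both arms) and one covariate of AUC 0.70, the adjusted model rejected in 4.9% of trials.

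**Step 5: room in the model.** Expected events are 314 × 0.345 ≈ 108. Treatment, ten centre contrasts and four covariates make 15 terms, or 108/15 ≈ 7 events per term. That is workable for a short list and a reason to keep it short.

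**The case against.** The strongest objection is that the point rests on silence. A reader might infer that the model is fixed as treatment and centre only. The article does not say so. It is a condensed account, and a covariate list is often left to the SAP, which is not shown. This stands: if the SAP lists covariates, nothing needs to change. What remains is that the article states the model and its one adjustment factor, and a better-specified model can be built from data it already collects.

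A reader might also infer that strong predictors are being ignored. The article does not support that. It gives qualitative reasons to expect some association and no figure for its strength. Alcohol intake is only an estimate and is cut off from below by the entry threshold. Severity could work in more than one way: the sickest patients may never be awake to have an event, while survivors may be more or less agitated. A negative coefficient gains as much precision as a positive one, but a relation that is not monotone would leave a linear term with little to explain.

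Adjustment also has a price. It changes the odds ratio from a marginal to a conditional one, while the hypothesis of 42% against 27% is marginal, and it needs complete baseline data. Both can be handled by the reporting and missing-data rules proposed below.

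**Conclusion.** The point holds as an efficiency recommendation. The planned analysis is valid and reaches its 80% under its own assumptions. It would be wrong to conclude that the trial is underpowered for want of covariates, and the interim sample size review already addresses erosion of power by deaths. It would also be wrong to say that the centre-only model is biased towards the null. The difference between adjusted and unadjusted odds ratios comes from the non-collapsibility of the odds ratio; the marginal effect is not distorted.

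The likely gain is about 0 to 1 point of power for weak covariates, 2 to 4 points for moderate ones (R² about 0.05 to 0.11, AUC about 0.63 to 0.70), and roughly 6 to 12 points only if they are strong (R² 0.15 to 0.30). Nothing in the article tells us which applies. The case for adjustment is that there is no material power loss even at the bottom of the range.

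**What to change.** Before unblinding, and unless the SAP already does so:

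- State that the primary logistic model contains treatment, centre and a short fixed list of baseline covariates: age, weekly alcohol intake, and SOFA and/or IGSII, each as a continuous term. The primary test is that of the treatment coefficient in this model.
- Add a simple rule for missing baseline values, set without reference to treatment arm, so that no randomised patient drops out of the analysis for lack of a covariate.
- Report the standardised (marginal) risk difference from this model with its confidence interval, so that the result answers the 42% to 27% hypothesis directly.
- Keep the centre-only model as a sensitivity analysis.
- Leave the sample size as planned. The assumed gain should serve as protection and not as a reason to recruit fewer patients.

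The cost is a few sentences in the protocol or SAP. No new data, visits or patients are needed.

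### The Poisson model named for the number of agitation events makes no stated allowance for overdispersion, so its standard errors are very likely too small

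*Protocol article*

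**What the plan says.** The protocol article, under Secondary outcome measure, lists a count of agitation-related adverse events over the ICU stay, limited to 28 days from ICU admission. For this count the Statistics section states that "a Poisson regression model will be applied to compare the number of adverse events related to agitation, between the two treatment arms". It mentions no dispersion parameter, robust variance or exposure term. It does say that the analysis will be stratified by centre.

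The same section bears on how variable the count will be:

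- On case mix: "Our study will include patients whatever their severity".
- On early death: "Some patients may die before sedation interruption thus altering the power of the study".
- On time in the unit, which is itself an outcome: "Both length of ICU stay and mechanical ventilation will be compared with a log-rank test".

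The component events listed under Primary outcome measure include removal of devices, removal of restraints and aggression. All of these can recur in one patient.

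**The concern.** Naming a Poisson regression brings in its variance assumption, namely variance equal to mean given the covariates. The trial's own description works against that assumption. An agitated patient may pull several lines or restraints, while a patient who stays deeply sedated or dies early contributes a zero. Differences in severity and in days spent in the ICU spread the counts further.

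If the variance exceeds the mean by a factor φ, the model-based standard error of the log rate ratio is too small by √φ. Intervals are too narrow by the same factor on the log scale, and the test rejects a true null hypothesis more often than 5% of the time. At stake is the credibility of any claim, in either direction, about the number of agitation events.

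**Working it through.** **The plan's own figure.** The article gives no calculation for the count. Its only sample-size figure is for the binary primary outcome: 42% against 27%, "using a two-sided test with an α of 5 % and 80 % power", with the conclusion "As a result, 314 patients are needed". With p̄ = (0.42 + 0.27)/2 = 0.345,

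n per arm = [1.96·√(2·0.345·0.655) + 0.8416·√(0.42·0.58 + 0.27·0.73)]² / 0.15² = 156.5, rounded up to 157, or 314 in total.

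The figure reproduces exactly, and nothing below changes it.

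**Inputs for the count.**

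- From the article: 157 patients per arm, and 42% with at least one event on placebo. The 42% belongs to the primary outcome, which covers the treatment period. The count covers the ICU stay to day 28, so the 42% is only a stand-in.
- Assumed: negative binomial counts with dispersion k from 0 to 4. The article gives neither a mean count nor a dispersion.

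**Formulas.** With P(0) = (1 + kμ)^(−1/k) = 0.58:

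- variance/mean: φ = 1 + kμ = 0.58^(−k)
- mean: μ = (φ − 1)/k, or −ln 0.58 = 0.545 at k = 0
- true type I error of a nominal 5% Poisson Wald test: 2·[1 − Φ(1.96/√φ)]

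The simulated columns come from 20,000 null trials per row, with 157 patients per arm, the same distribution in both arms and no centre effect.

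| k | mean μ | events per affected patient (μ/0.42) | φ | SE too small by √φ | type I error, formula | simulated, Poisson | simulated, robust variance |
|---|---|---|---|---|---|---|---|
| 0 | 0.545 | 1.30 | 1.00 | 1.00 | 5.0% | 5.0% | 5.2% |
| 0.5 | 0.626 | 1.49 | 1.31 | 1.15 | 8.7% | 8.7% | 5.4% |
| 1 | 0.724 | 1.72 | 1.72 | 1.31 | 13.6% | 13.3% | 5.6% |
| 2 | 0.986 | 2.35 | 2.97 | 1.72 | 25.6% | 25.3% | 5.3% |
| 4 | 1.959 | 4.66 | 8.84 | 2.97 | 51.0% | 51.0% | 6.1% |

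With 34.5% of patients affected instead of 42%, the simulated Poisson errors are 4.9%, 7.9%, 11.3%, 20.2% and 39.7%.

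**Two sources taken alone** (42% affected in both):

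- *Unequal ICU time.* Assume log-normal stays with median 10 days and log-SD 0.5 to 1.0, capped at 28 days, the same in both arms and with a constant daily event rate. Then φ is 1.14 to 1.32 and the simulated error is 6.4% to 8.4%.
- *Patients never at risk.* For an assumed share π of 10%, 20% or 30%, let λ be the mean among the rest. Then (1 − π)(1 − e^(−λ)) = 0.42 gives λ = 0.629, 0.744 or 0.916. With φ = 1 + πλ = 1.06, 1.15 or 1.27, the error is about 5.7%, 6.7% or 8.3%.

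Each source alone has a modest effect. The large values in the table need repeated events concentrated in a minority of patients.

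**The case against.** The strongest objection is that a condensed article gives this outcome one sentence. Dispersion and variance estimation are commonly left to the analysis plan, which is not shown, and Poisson regression with a sandwich variance is still Poisson regression. A reader might infer that the trial ignores overdispersion; the article does not show that. What remains is that it has already chosen a model family whose default variance is ill-suited to this count, and a better choice is available at almost no cost.

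The size can also be challenged, and that objection stands. The 58% without events is borrowed from an outcome with another window. Nor does a mean above 0.545 by itself prove overdispersion. With 58% zeros, 25% ones and 17% twos, the mean is 0.25 + 2·0.17 = 0.59 and the variance is (0.25 + 4·0.17) − 0.59² = 0.58, just below the mean. The inference needs a mixed-Poisson form such as the negative binomial.

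Two stronger readings are tempting.

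- *The results will be too favourable to baclofen.* Understated standard errors produce excess false positives in both directions. A difference in ICU time between arms can also push either way: at equal daily event rates, a mean-stay ratio of 0.8 (baclofen to placebo) gives an event ratio of about 0.8, and a ratio of 1.2 gives about 1.2.
- *Log ICU time must be an offset.* Events per patient to day 28 is a coherent intention-to-treat quantity. ICU stay arises after randomisation and is a listed outcome. The Discussion expects less agitation to reduce other hypnotics and, with them, ventilation time. Dividing by ICU days changes the question and could hide a benefit.

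**Conclusion.** The point holds for the variance assumption. Overdispersion is very likely, given recurrent events, unrestricted severity, early deaths and variable ICU time. If it is present, uncorrected Poisson standard errors and intervals for this outcome are too small. Its extent cannot be fixed from the article. Under the negative binomial assumption with 42% affected, the type I error runs from 5% with no overdispersion to about 50% at k = 4, and is about 9% to 25% for k between 0.5 and 2. These figures illustrate a range and do not predict a value.

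The absence of an ICU-time offset is not an error, because including one is a choice of estimand. The matter concerns one secondary outcome. The primary logistic regression and the total of 314 stand as they are.

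**What to change.** Specify, before unblinding, negative binomial regression for the number of agitation events, or Poisson regression with a robust (sandwich) variance. Keep the centre stratification already stated. Define the main estimand as events per patient during the ICU stay up to day 28. A rate per ICU day, with log ICU time as offset, may be added as a supportive analysis, with a note that treatment may itself change ICU stay.

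This costs about one sentence and uses standard software. The downside is wider intervals when counts are overdispersed; if they are not, the results will be close to those of the ordinary Poisson model. In the simulations the robust variance kept the type I error between 5.0% and 6.1%, slightly liberal at k = 4.

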### Population

At ICU admission, patients with a mechanical ventilation (MV) duration expected to be equal to or longer than 24 h may be included.

For patients with tracheal intubation at ICU admission:If intubation was performed less than 48 h before admission, inclusion can be performed within 24 h after admissionIf intubation was performed 48 h or more before admission, inclusion cannot be performed

For patients without tracheal intubation at ICU admission:If intubation was performed within the first 48 h after admission, inclusion can be performed in the first 24 h after intubationIf intubation was performed at or after 48 h, inclusion cannot be performed

All patients, whatever the severity of organ failure, would be eligible for screening inclusion.

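### The log-rank comparisons of ICU stay and ventilation duration do not say how death enters; counting death as the end of stay can make excess early mortality look like a shorter stay, and censoring it leaves live discharge unanswered

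*Protocol article*

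**What the plan says.** For the two durations, the Statistics section of the protocol article names the test and nothing more: "Both length of ICU stay and mechanical ventilation will be compared with a log-rank test". It does not state whether death is an event, a censoring or a competing event.

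The protocol does expect deaths. Under Population: "All patients, whatever the severity of organ failure, would be eligible for screening inclusion". Under Statistics: "Our study will include patients whatever their severity", followed by "Some patients may die before sedation interruption thus altering the power of the study". No mortality rate is given.

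The only stated handling of deaths belongs to the agitation outcome: "Two sensitivity analyses will be performed and will consider dead patients to be without agitation, or as patients with or without agitation". The list of secondary outcomes also contains ventilation-free days at day 28, a composite of agitation events with 28-day mortality, and death in the ICU, at days 28 and 90, and during the hospital stay. It contains no outcome that combines ICU stay with survival.

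**The concern.** A patient can stop being ventilated, or stop occupying an ICU bed, by recovering or by dying. A plain log-rank test has one kind of event, so each death must be either that event or a censoring.

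- **Death as the event.** Dying on day 3 and being discharged well on day 3 count the same. An arm with more early deaths empties faster and looks better.
- **Death as censoring.** The test compares the rate of live discharge (or extubation) among patients still in the ICU (or still ventilated). It does not register that fewer patients ever reach that point alive.

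The abstract names both durations first among the secondary outcomes, and the Discussion presents less time on the ventilator as an expected benefit. A falsely shorter duration would seem to support that argument.

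**Working it through.** **1. The plan's own figure.** The design inputs are "using a two-sided test with an α of 5 % and 80 % power, from 42 to 27" %, and the section concludes "As a result, 314 patients are needed". With pooled variance under the null, p̄ = (0.42 + 0.27)/2 = 0.345 and

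n per arm = [1.960·√(2·0.345·0.655) + 0.842·√(0.42·0.58 + 0.27·0.73)]² / 0.15² = 156.5, rounded up to 157.

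The total is 314, as stated. The log-rank comparisons have no figure of their own, so 157 per arm (1:1 allocation) is used below.

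**2. Assumed inputs.** The documents give no mortality or discharge rate, so these are assumptions: live discharge λ = 0.07 per day in both arms; ICU death δ = 0.025 per day on placebo, multiplied by 1.3, 1.5 or 2 in the other arm; constant rates; follow-up cut at day 28. ICU death by day 28 is δ/(λ+δ)·[1 − exp(−28(λ+δ))]. On placebo this is 0.025/0.095·(1 − e^−2.66) = 24%.

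**3. Death counted as the end of stay.** The hazard of leaving for any reason is λ + δ, so the hazard ratio between arms is (0.07 + δ₁)/0.095. The expected log-rank Z is about ln(HR)·√(events/4), and the chance of a significantly shorter stay is P(N(0,1) > 1.96 − Z).

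| Death rate multiplied by | ICU death by day 28 | HR of leaving | Expected events | Expected Z | Falsely shorter, formula | Falsely shorter, 4,000 simulated trials |
|---|---|---|---|---|---|---|
| 1.3 | 30% | 0.1025/0.095 = 1.079 | 294 | 0.65 | 9.5% | 9% |
| 1.5 | 33% | 0.1075/0.095 = 1.132 | 295 | 1.06 | 18.5% | 18% |
| 2 | 40% | 0.12/0.095 = 1.263 | 298 | 2.02 | 52% | 52% |

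The nominal rate in this direction is 2.5%. Recovery is identical in both arms by construction.

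**4. Death censored, same inputs.** The simulated rate stays at about 2.5% in each direction, whatever the mortality.

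**5. Deaths kept in the risk set to day 28 as never discharged (a competing-event type of analysis).** Significantly slower live discharge is found in about 10%, 16% and 45% of trials. The share discharged alive by day 28 is λ/(λ+δ)·[1 − exp(−28(λ+δ))]: 69% on placebo, against 64%, 62% and 56%.

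**6. A second set of assumptions.** Recovery time is exponential with median 10 days in both arms, a fixed share of patients is prone to die with mean time to death 5 days, and each scenario has 3,000 runs. Figures in brackets let sicker patients both stay longer and die more.

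| Share prone to die | Death as event: falsely shorter | Death censored: falsely shorter | Deaths kept in risk set: slower live exit |
|---|---|---|---|
| 30% vs 20% | 13% (18%) | 3.0% (3.8%) | 18% (13%) |
| 40% vs 20% | 35% (54%) | 2.8% (5.8%) | 53% (36%) |

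Without that dependence, the observed median duration is 7.6 days in the 20% arm and 6.5 or 5.6 days in the arm with more deaths, with no true effect on recovery.

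**The case against.** The strongest reply is that the distortion in step 3 needs a coding the article never states. Event and censoring definitions are normally left to a statistical analysis plan, which is not shown, and a log-rank test with discharge alive as the event is possible. A reader might infer that the plan counts death as the end of stay. The document does not say so, and that reading is not asserted here.

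A reader might also infer that censoring deaths makes the test invalid. It does not. When death is unrelated to recovery, the censored test is a sound comparison of cause-specific live-discharge rates. The slower live discharge in step 5 comes entirely from mortality, because the discharge rates were set equal. That is a different question, not a corrected answer to the same one.

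Nor would harm necessarily be hidden. Mortality is a listed outcome, and binary secondary outcomes are tested by logistic regression. In the scenarios of step 3, a two-proportion test of ICU death would be significant in about 19%, 40% and 85% of trials, more often than the falsely shorter stay.

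Finally, the protocol says only that some patients may die. It caps age at 70 and excludes patients with care limitations for poor prognosis and those with resuscitated cardiac arrest. That many will die ventilated is not supported by the text.

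All of this limits the point. What remains is that the test itself is fixed in the document, and neither coding of a plain log-rank test shows how many patients leave or are extubated alive, and when.

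**Conclusion.** The point holds in conditional form, as a change that should be made to two secondary analyses.

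- **If death is the event:** a falsely shorter duration is declared in roughly 9% to 54% of trials across the scenarios above, against 2.5%. The upper end needs a doubled death rate or 20 points more patients prone to die.
- **If death is censored:** inflation is absent or small (at most 5.8%, when sicker patients both stay longer and die more). The remaining fault is one of interpretation.

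Every mortality and discharge figure is an assumption; the direction of the distortion under the first coding does not depend on them. The gap is widest for ICU stay. For ventilation, the planned ventilation-free days and mortality outcomes give partial cover. The primary analysis and the sample size of 314 do not change.

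**What to change.** Define the two events as ICU discharge alive and successful extubation alive, both timed from randomisation, with death as a competing event. Compare cumulative incidences with Gray's test or a Fine-Gray model, stratified by centre as the Statistics section already intends. Report the cause-specific hazards alongside, so that a change in recovery rate can be told apart from a change in mortality. Present both results next to the ventilation-free days and mortality outcomes already planned.

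The cost is a few sentences of plan text, settled before unblinding, and a standard procedure. Stay, ventilation and death are already collected. The downside is that the subdistribution hazard ratio is less familiar to readers and mixes mortality into the effect, which is why the cause-specific results belong beside it.

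### For ICU-acquired infection and tracheotomy, the yes/no odds ratio alone cannot separate prevention from early death; report cumulative incidence of the event and of death alongside it

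*Protocol article*

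**What the plan says.** The secondary outcome list of the protocol article includes infections acquired in the ICU (urinary, pneumonia, catheter, bacteraemia) and tracheotomy because weaning failed. Several neighbouring outcomes carry a 28-day window from ICU admission; these two carry none.

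The Statistics section assigns Poisson regression to the number of agitation events and a log-rank test to ICU stay and ventilation. For the rest it says: "Logistic regression will be used to compare binary qualitative secondary endpoints". Infection and tracheotomy, as yes/no outcomes, fall under that sentence. The analysis set is also fixed: "Statistical analysis will take place on an intention-to-treat principle".

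On severity and death, the Population section says: "All patients, whatever the severity of organ failure, would be eligible for screening inclusion". The Statistics section repeats that "Our study will include patients whatever their severity" and adds: "Some patients may die before sedation interruption thus altering the power of the study". Death is then handled for agitation: "Two sensitivity analyses will be performed and will consider dead patients to be without agitation, or as patients with or without agitation". The secondary outcomes also include a composite of agitation events or 28-day mortality. No companion measure of that kind is given for infection or tracheotomy. Death in the ICU, at days 28 and 90, and during the hospital stay are separate secondary outcomes.

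**The concern.** A patient can acquire an ICU infection only while alive in the ICU, and can have a tracheotomy for weaning failure only after some time on the ventilator. Death ends the chance of either. In a yes/no analysis of everyone randomised, a patient who dies early and event-free would be counted in the same way as one who recovers without the event.

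If one arm has more early deaths, it will show fewer infections and tracheotomies even when treatment affects neither risk. An odds ratio below 1 could then mean easier weaning or less time for the event to occur, and that number alone does not say which. The protocol expects early deaths and provides for them in the agitation outcomes, so the gap for these two endpoints is uneven as well as avoidable.

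**Working it through.** **Plan's own figure.** The sample size rests on "using a two-sided test with an α of 5 % and 80 % power, from 42 to 27" per cent, giving "As a result, 314 patients are needed". With pooled variance and mean proportion 0.345:

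n per arm = [1.960·√(2·0.345·0.655) + 0.842·√(0.42·0.58 + 0.27·0.73)]² / 0.15² = 156.5, rounded up to 157, so 314 in total.

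This reproduces exactly and is not in dispute. It supplies the 157 per arm used below.

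**Inputs for the illustration.** The documents give no infection, tracheotomy or mortality rate, so everything in this step is assumed:
- infection hazard 2% per ICU day in both arms;
- 12 ICU days in survivors and 4 in those who die;
- tracheotomy in 15% of survivors and in none of the early deaths;
- mortality m of 20% in one arm, and 20 to 35% in the other.

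Treatment has no effect on either risk by construction.

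**Formulas.**
- Infection: (1−m)(1−e^(−0.02·12)) + m(1−e^(−0.02·4)) = 0.2134(1−m) + 0.0769m
- Tracheotomy: 0.15(1−m)

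For m = 0.20, infection is 0.1707 + 0.0154 = 0.186 and tracheotomy is 0.120. For m = 0.30, infection is 0.1494 + 0.0231 = 0.172 and tracheotomy is 0.105.

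| Mortality | Infection | OR | Tracheotomy | OR |
|---|---|---|---|---|
| 20 v 20% | 18.6 v 18.6% | 1.00 | 12.0 v 12.0% | 1.00 |
| 20 v 25% | 18.6 v 17.9% | 0.96 | 12.0 v 11.3% | 0.93 |
| 20 v 30% | 18.6 v 17.2% | 0.91 | 12.0 v 10.5% | 0.86 |
| 20 v 35% | 18.6 v 16.6% | 0.87 | 12.0 v 9.8% | 0.79 |

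The infection hazard among patients still at risk is the same in both arms throughout, so a cause-specific hazard ratio for infection would be 1.

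**Second model, infection only.** Take constant hazards over 28 days, with a 30% infection risk if nobody died. Then h_i = −ln(0.70)/28, h_d = −ln(1−m)/28, and the proportion infected is h_i/(h_i+h_d)·(1−e^(−28(h_i+h_d))).
- Mortality 20 v 30%: 27.1 v 25.5%, OR 0.92 (0.91 to 0.93 as the infection risk runs from 20 to 40%).
- Mortality 20 v 40%: 27.1 v 23.9%, OR 0.84 (0.83 to 0.86 over the same range).

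**Outer bound.** If every death came before any infection could occur, the proportion is 0.30(1−m).
- 20 v 30%: 24 v 21%, OR 0.84.
- 20 v 40%: 24 v 18%, OR 0.70.

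**What this means at 157 per arm.** In the 20 v 30% row of the table, the shift is 157·(0.1861−0.1724) ≈ 2 infections and 157·(0.120−0.105) ≈ 2 tracheotomies. The 95% intervals are about 0.51 to 1.62 for the infection OR and 0.43 to 1.74 for the tracheotomy OR. By a pooled two-proportion test, the chance of a significant result favouring the arm with more deaths is about 5 to 6%, against a nominal 2.5%. At 20 v 35% it is about 7 to 9%. The outer bound gives about 9% and 26% for its two scenarios.

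**The case against.** The strongest reply is that the method is not wrong. With complete follow-up, the proportion of randomised patients who acquire an infection is the cumulative incidence with death competing, which is a proper intention-to-treat quantity. That stands: the weakness lies in what the odds ratio can show when read alone.

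Second, the article never says how a death is coded for these endpoints. That also stands, and the 'no' coding is an inference. It is the natural one, because leaving the dead out would depart from intention to treat. A patient infected or tracheotomised before dying still counts as an event.

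Third, mortality is reported separately. In the 20 v 30% scenario the same pooled two-proportion test at 157 per arm would find the mortality difference significant about 53% of the time. A reader would often be warned, but a warning does not show how much of a lower infection count is due to death.

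Fourth, putting a cause-specific hazard ratio in place of the logistic model would be a trade. The Discussion hopes for shorter ventilation. If treatment prevented infections by shortening exposure, that ratio could sit at 1 and hide a benefit that the proportion shows. This stands, and it is why the logistic comparison should stay.

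A reader might go further and infer that the plan uses an invalid analysis that rewards harm. The documents do not support that. They give no mortality rates and no reason to expect a large difference between arms, and with equal early mortality the distortion vanishes.

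**Conclusion.** The point holds as a modest gap in two secondary endpoints. The stated analysis is valid for the cumulative incidence, but it comes with no companion measure that would let a lower odds ratio be read as prevention, although the protocol expects early deaths and deals with them for agitation.

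The direction is clear if early mortality differs: the arm with more early deaths looks better. The size depends entirely on assumed rates. At 20 v 30% mortality it is about two patients per endpoint, with odds ratios near 0.91 and 0.86. Larger mortality gaps or earlier deaths give more, and equal mortality gives nothing. The conclusion also rests on event-free deaths being coded 'no', which is inferred. The primary outcome and the 314 patients are not touched. This is a worthwhile low-cost improvement, not a fault that threatens the trial.

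**What to change.** Keep logistic regression for both endpoints and state how a patient who dies without the event is coded. Fix a common time window, for example the 28 days used for other outcomes, and state its origin, since those outcomes count from ICU admission.

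Then add, for each endpoint:
- the cumulative incidence by arm of the event and of death without the event, measured from randomisation;
- the centre-stratified cause-specific hazard ratio.

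For infection, the competing events are death and ICU discharge. For tracheotomy, they are death and successful extubation; plain extubation will not do, because reintubation within 48 hours is itself an outcome.

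The Track record section already provides for recording acquired infection, ventilation and ICU stay, with outcomes notified daily, and death is among the outcomes. The cost is some plan wording, modest programming and a few more estimates to read. It is best settled before unblinding.
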